### 1.5. Proposed Research Aims and Objectives

The general objective of the research is to determine whether or not GT is an effective treatment for depression in PWD.

Specific objectives of the study are:-To assess if there is a pre/post improvement and, if so, how great this is (clinical significance), according to the outcome variables rates, as well as whether it can be attributed to the therapy intervention.-To assess if study participants suffer with loneliness.-To assess if loneliness is mitigated by the regular contact with the therapist.-To assess if the regular contact with the therapist affects the level of depression.-To assess if a clinical improvement of depression symptoms has an indirect effect on the level of family carers’ burden.-To assess if a clinical improvement has an indirect effect on the mutuality of the relationship between the patient and the family carer.

In order to achieve the objectives, the following research questions will need to be answered:Is there any pre/post treatment improvement?If the answer to question 1 is yes, is the change clinically significant (reduction of symptoms by 50%)?If loneliness is a factor, is the improvement solely due to the social contact with the therapist? ORCan the improvement be attributed to the therapy intervention?Can the improvement of the patient also have an impact on the caregiver’s burden and level of mutuality?

The researchers hypothesised that: depressive symptoms will improve post GT treatment and the improvement will be maintained at follow-up; the level of loneliness, if a factor, can decrease post-treatment and remain so at follow-up; the improvement of symptoms is related to the GT treatment; the level of burden of the family carer will reduce whilst the mutuality in the relationship will increase as the PWD’s depression improves.

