## 2. Materials and Methods

### 2.1. Research Design

The ABA single-case experimental design will be used for the purpose of the study, as explained previously.

The research method is divided into three phases: an “A” baseline period of two weeks between the assessment session “0” and initial psychotherapy session; a “B” intervention period of minimum eight GT sessions; an “A” follow-up period of six months after the end of the intervention, with measurements at the final session, after two weeks and six months. More specifically, in relation to data collection, the following will happen in each phase: A—at the baseline, outcome measures will be administered at session “0”, and individual target complaints (TC) will be recorded daily for the following two weeks; B—in the intervention phase, target complaints will be completed daily; A—in the follow-up phase, participants will continue with daily assessment for another two weeks, while outcome measures will be administered at the final session, i.e., week two and week twenty-four (Figure 1).

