### 2.4. Measures and Data Collection Tools

Overall, data will be collected through questionnaires and audio/video recording. Outcome measures will gather quantitative data on the symptoms, quality of life, level of loneliness, family carers’ burden, and mutuality and will be administered at session “0”, at the final session and follow-up (week 2 and week 24), whilst target complaints will be repeated daily and used for the time series analysis. All the measures and related administration time points are shown in Table 1 and described below.

The Neuropsychiatric Inventory Questionnaire (NPI) was developed by Cummings et al. [73] and validated by Binetti et al. [74] for the Italian population and by Zepeda et al. [75] for the Mexican population. It measures the behavioural symptoms related to dementia conditions, assessing twelve sub-domains: delusions, hallucinations, agitation/aggression, depression/dysphoria, anxiety, elation/euphoria, apathy/indifference, disinhibition, irritability/lability, motor disturbance, night-time behaviours, and appetite/eating. Additionally, a caregiver distress scale was included for measuring the psychological impact of the neuropsychiatric symptoms on family caregivers [76]. The NPI anxiety (NPI-A) score will be used to assess the level of anxiety of participants at pre/post treatment. The test has good internal consistency, content validity, and inter-rater/test-retest reliability.

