### 2.5. Data Analysis

Continuous variables will be analysed and reported as mean ± SD (standard deviation) or median and IQR (interquartile range), on the basis of their distribution (assessed through Shapiro–Wilk test). Discrete variables will be reported as absolute frequencies and percentage.

In order to evaluate any pre/post improvements (from baseline to follow-up: at the final session, after two weeks and twenty-four weeks following the end of the treatment) in the main outcomes, i.e., depression and anxiety symptoms (GDS; NPI-A), quality of life (QOL-AD), and the therapy outcome (CORE–OM), three types of analysis will be carried out: (a) visual analysis, comparing the target complaint (TC) scores during the three phases; (b) mean difference from baseline to follow-up tested, by means of paired t-test or Mann–Whitney U test, according to the distribution of the outcome variable [99]; (c) mean baseline reduction (MBLR) for obtaining the effect size for single-case designs [100,101,102], as follows:MBLR = (Mean of Baseline phase − Mean of Follow-up phase) × 100/Mean of Baseline phase.(1)

The same procedure will be applied for the secondary outcome, i.e., loneliness. Additionally, data collected from family caregivers (i.e., QOL-AD family version, caregiver burden scale, and the mutuality scale) during the three phases of the study will be compared with subjects’ outcomes, in order to evaluate indirect effects of the treatment, by means of Pearson or Spearman correlation coefficients, as appropriate.

Blind raters will assess the fidelity of the approach by rating a small sample of sessions through the GTFS.

A two-tailed *p* value < 0.05 will be considered significant. Data will be analysed using SPSS for Windows V24.0 (SPSS Inc., Chicago, IL, USA) and Simulation Modeling Analysis (SMA) for Windows V07.30.20 (ClinicalResearcher, Jeff Borckardt, Medical University of South Carolina).

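### MBLR uses one undated follow-up mean, and the article defines follow-up in two ways, so the effect size cannot separate end-of-therapy improvement from maintenance at week 24

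*Protocol article*

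**What the plan says.** **Effect size.** Section 2.5 (Data Analysis) gives one formula for the depression, anxiety, quality-of-life and therapy outcomes: "MBLR = (Mean of Baseline phase − Mean of Follow-up phase) × 100/Mean of Baseline phase". Its follow-up term, "Mean of Follow-up phase", carries no time index.

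**What follow-up contains, first version.** Section 2.1 (Research Design) describes a six-month follow-up phase "with measurements at the final session, after two weeks and six months". Section 2.5 lists the same three points when it describes the pre/post comparison: "from baseline to follow-up: at the final session, after two weeks and twenty-four weeks following the end of the treatment".

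**What follow-up contains, second version.** Section 2.4 (Measures and Data Collection Tools) schedules the outcome measures "at the final session and follow-up (week 2 and week 24"), which keeps the final session outside follow-up. Table 1 does the same for GDS, NPI-A, QOL-AD and CORE-OM.

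**Claims to be supported.** Section 1.5 hypothesises that "depressive symptoms will improve post GT treatment and the improvement will be maintained at follow-up". Its second research question asks "is the change clinically significant (reduction of symptoms by 50"%). No time point is attached to the 50%, and MBLR is not mentioned there.

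**The concern.** Section 1.5 makes two claims: that symptoms improve after therapy, and that the improvement lasts. GDS, NPI-A, QOL-AD and CORE-OM each have a single score at session 0 and a single score at each later visit. If all three later visits belong to the follow-up phase, as Sections 2.1 and 2.5 say, the follow-up mean is the average of three scores. Two-thirds of its weight then falls within two weeks of the end of therapy and one-third on week 24. One such number cannot show which claim it supports. It can look good after a relapse, and it can look poor when a real response at the end of therapy has later faded.

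This matters because the study has 12 patients and no control arm. Per-patient effect sizes, and a judgement of clinical significance, will carry much of the conclusion. Which visits enter the mean can change which patients count as improved by half, so the choice should be settled before any data are seen.

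**Working it through.** The article states no expected MBLR and no responder rate, so there is no figure of its own to reproduce. The check applies its formula to GDS.

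**Inputs.** The formula is from Section 2.5. The three follow-up points are from Sections 2.1 and 2.5, and the two-point alternative is from Section 2.4 and Table 1. The 50% criterion is from Section 1.5. The baseline GDS range of 10 to 19 is from the inclusion criteria in Section 2.3 (entry on anxiety alone is also possible). The patient scores below are illustrative.

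**Notation.** B is the session 0 score, F the final session, W week 2 and L week 24.

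**Three-point reading.**
MBLR = 100 × [B − (F + W + L)/3] / B, which equals the plain average of the three visit reductions.
With full relapse, L = B, so MBLR = 100 × [2/3 − (F + W)/(3B)].
This is at least 50% exactly when F + W ≤ B/2, that is, when the mean reduction at the final session and week 2 is at least 75%.

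**Two-point reading (week 2 and week 24).**
With L = B, MBLR = 100 × [B − (W + B)/2] / B = 50 × (1 − W/B).
The maximum is 50.0%, reached only when W = 0.

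**Worked cases.**

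| GDS: B, then F, W, L | Reduction at F / W / L | Three-point MBLR | Two-point MBLR |
|---|---|---|---|
| 16, then 4, 4, 16 | 75% / 75% / 0% | 50.0% | 37.5% |
| 16, then 4, 5, 14 | 75% / 68.75% / 12.5% | 52.1% | 40.6% |
| 16, then 8, 8, 16 | 50% / 50% / 0% | 33.3% | 25.0% |
| 12, then 3, 3, 12 | 75% / 75% / 0% | 50.0% | 37.5% |
| 19, then 4, 4, 19 | 78.9% / 78.9% / 0% | 52.6% | 39.5% |

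For example, row 2: (16 − 23/3)/16 = 52.1% on three points, and (16 − 19/2)/16 = 40.6% on two.

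**Range.** With full relapse at week 24 and equal reductions at the first two visits, the three-point MBLR is:

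| Early reduction | 50% | 60% | 70% | 75% | 80% | 90% | 100% |
|---|---|---|---|---|---|---|---|
| MBLR | 33.3% | 40.0% | 46.7% | 50.0% | 53.3% | 60.0% | 66.7% |

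Enumerating whole-number scores shows that at every baseline from 10 to 19 some fully relapsed patient reaches 50% or more on three points.

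**Daily target complaints.** Section 2.1 gives two weeks of daily ratings after therapy. A phase mean suits such a series. A fall from 8 to 4 over those 14 days gives 50.0% whatever happens later, so this series does not speak to week 24.

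**Per visit.** For 16, then 4, 4, 16, separate figures are 75%, 75% and 0%. The early response and the relapse are both visible.

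**The case against.** A reader might infer that the plan averages the three visits outright and would declare a relapsed patient clinically improved. The documents do not go that far.

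- **Pooling is not stated in words.** The list of times in Section 2.5 can also be read as three separate comparisons with baseline. This stands as a limit on the claim. The formula, however, has one follow-up term, and Section 2.1 places all three measurements in that phase, so pooling is the literal reading.
- **Section 2.4 and Table 1 point the other way.** On their definition a fully relapsed patient passes only with a score of 0 at week 2, so false success after full relapse all but disappears. This also stands. The mean would still mix an early score with a late one.
- **The 50% criterion is not tied to MBLR.** Correct. The link is an inference from MBLR being the only percentage-reduction statistic in the plan.
- **MBLR is one of three analyses and is offered as an effect size.** Nothing says the maintenance hypothesis is judged on it. That stands too. The other two do not clearly fill the gap: the visual analysis concerns target complaints, and the baseline-to-follow-up test is not clearly assigned to a visit.
- **Pooling is not uniformly lenient.** For a relapsing patient with an early response of 50% to just under 75%, it is stricter than a rule applied at the end of therapy.
- **An article leaves detail to a fuller document.** True in general, but this article prints the formula and gives two different accounts of the phase on which the formula depends.

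**Conclusion.** The concern holds in a conditional form. The article fixes an effect size with a single follow-up mean and describes the content of that mean in two incompatible ways. On either description the figure blends early and late scores and cannot, alone, distinguish improvement after therapy from maintenance at week 24.

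The size depends on two assumptions: that the three visits are pooled, as Sections 2.1 and 2.5 literally imply, and that the 50% criterion is applied to MBLR. Under both, full relapse by week 24 is compatible with meeting 50% whenever the mean reduction at the first two visits is at least 75%. A relapsing patient who had halved the score at those visits gets 33.3%. On the two-point definition, full relapse can reach 50% only from a week 2 score of 0.

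The documents do not support saying that the plan will classify relapsed patients as responders, or that maintenance will be tested by MBLR. They support saying that the effect size is badly fixed for the claims it accompanies and should be corrected before data are seen.

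**What to change.** 1. Reconcile Sections 1.5, 2.1, 2.4, 2.5 and Table 1 on whether the final session belongs to follow-up, and use one definition throughout.
2. For GDS, NPI-A, QOL-AD and CORE-OM, compute and report MBLR separately at the final session, week 2 and week 24, each against the session 0 score.
3. State in advance the time point at which the 50% criterion is judged, and whether MBLR at that point is the statistic used. Use week 24 for the maintenance claim.
4. Keep the phase-mean form of the formula only for the daily target complaint series, and say which days make up its follow-up mean.

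**Cost.** Wording only. No new data or visits are needed. Each outcome will have three figures in place of one, and the week 24 figure may be less favourable than a pooled one.

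### The hypothesised fall in carer burden and rise in mutuality has no test: Section 2.5 gives the carer scales only a correlation with patient outcomes, which cannot show a mean change

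*Protocol article*

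**What the plan says.** **The hypothesis (protocol article, Section 1.5).** The researchers expect that "the level of burden of the family carer will reduce whilst the mutuality in the relationship will increase as the PWD’s depression improves". Two of the six specific objectives (burden and mutuality) and the last research question concern this. The Discussion also anticipates lower stress or burden in carers.

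**The pre/post test (Section 2.5).** The main outcomes are GDS, NPI-A, QOL-AD and CORE–OM. For these the plan gives a "mean difference from baseline to follow-up tested, by means of paired t-test or Mann–Whitney U test", alongside visual analysis and the mean baseline reduction. It is then extended to one further outcome: "The same procedure will be applied for the secondary outcome, i.e., loneliness".

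**The carer analysis (Section 2.5).** What carers report on the mutuality scale, the burden scale and the family version of QOL-AD across all three phases is set against the patients' results "in order to evaluate indirect effects of the treatment, by means of Pearson or Spearman correlation coefficients". The sentence does not say whether scores or changes are correlated, or how the visits are combined. No other analysis is assigned to burden or mutuality.

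**Timing (Section 2.4 and Table 1).** The carer scales are collected at session 0, the final session and follow-up (weeks 2 and 24), which makes four occasions.

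**The concern.** The hypothesis is about direction: burden goes down and mutuality goes up. The named method answers a different question, namely whether dyads with higher patient scores also have higher or lower carer scores. The article fixes both the method and its purpose, so this is a mismatch in what is written and not a detail left for later.

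Errors in both directions are at stake. A real, uniform fall in burden would leave no trace in the coefficient. Conversely, Section 1.1 itself links carer burden to behavioural or depressive symptoms in dementia, without reference to therapy. Such a standing association could be reported as an indirect effect of Gestalt therapy although no carer had changed.

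**Working it through.** **1. What the plan's own figure covers.** The only size figure is the 12 patients in Section 2.3, taken from a recommended 4 to 10 cases and raised for 20–30% dropout. It can be reproduced as 9/(1 − 0.20) = 11.25, rounded up to 12, or 8/(1 − 0.30) = 11.4, rounded up to 12. Completers would number 12 × 0.70 = 8.4 to 12 × 0.80 = 9.6. This is not a power calculation and says nothing about the carer correlation.

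**2. The main point, which needs no assumption.** Let P be the patient score and C the carer score, with one value per dyad.
- Scores: r(P + a, C + b) = r(P, C) for any constants a and b.
- Changes: r(ΔP + a, ΔC + b) = r(ΔP, ΔC).

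The coefficient is the same whether mean burden fell, stayed or rose. If visits were stacked, a shared shift over time would move the coefficient, but both scores worsening together would move it exactly as both improving would. That does not test a fall either.

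**3. Size if scores are correlated at one visit.** Inputs from the article: 12 dyads, two-sided 0.05. Inputs assumed, because the documents give none: a correlation ρ between the stable parts of the two scores, and an ICC (the stable share of variance).
- Critical |r| = t/√(n − 2 + t²). For n = 12: 2.228/√(10 + 4.965) = 0.576. For n = 9 it is 0.666 and for n = 8 it is 0.707.
- With ρ = 0.5 the expected observed correlation is ρ × ICC, which is 0.35 at ICC 0.7 and 0.40 at ICC 0.8.
- Fisher approximation to the chance of significance, Φ(atanh(r)·√(n − 3) − 1.96): for r = 0.35, Φ(0.365 × 3 − 1.96) = Φ(−0.86) = 0.19. For r = 0.40, Φ(0.424 × 3 − 1.96) = Φ(−0.69) = 0.25.
- Simulation agrees: about 20% at ICC 0.7 and 26% at ICC 0.8.

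Chance of a significant result by simulation when nobody changes (ICC 0.8, 20,000 runs per setting):

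| ρ | Score correlation, final session, n = 12 | Same, n = 9 | Change-on-change correlation | Paired t-test on carer score |
|---|---|---|---|---|
| 0 | 5% | 5% | 5% | 5% |
| 0.3 | 12% | 9% | 5% | 5% |
| 0.5 | 26% | 18% | 5% | 5% |
| 0.7 | 51% | 37% | 5% | 5% |

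At ρ = 0.5 and n = 12, the range over ICC 0.5 to 0.8 is 12 to 26%.

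**4. The coefficient does not respond to what the carer does.** For ρ = 0.5, n = 12 and ICC 0.8, the final-session correlation is significant in about 26% of runs in each of three cases: nobody changes, the patient improves by 1 SD and the carer does not change, or the patient improves by 1 SD and the carer worsens by 1 SD.

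**5. The missed effect.** Suppose both scores fall by 1 SD in every dyad and ρ = 0. The final-session correlation is significant in 5% of runs, and so is the change-on-change correlation. A paired t-test on the carer score detects the fall in 99.9% (n = 12). By hand, the SD of change is √(2 × 0.2) = 0.632, and 1/(0.632/√12) = 5.5 standard errors.

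**The case against.** **Scores or changes.** The text does not say that raw scores are correlated, and the preceding sentences of Section 2.5 deal with baseline-to-follow-up differences. This stands. If changes were meant, the false signal in step 3 drops to about 5%. Steps 2 and 5 are untouched, because a correlation of changes does not test a mean fall either.

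**Pooling.** A reader might infer that four visits from 12 dyads would be stacked as 48 independent rows. With ρ = 0.5 the correlation would then be significant in roughly 61 to 69% of studies in which nobody changes (ICC 0.7 to 0.8), and in 23 to 27% with ρ = 0. The article does not say that visits are stacked, so these figures describe one possible reading and not the plan.

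**An effect when nothing moved.** A reader might also infer that the plan could claim an indirect effect when neither depression nor burden changed. That goes too far. Depression is tested separately, and the carer question in Section 1.5 starts from an improvement in the patient. The exposed case is the patient who improves while the carer does not.

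**Not a type I error.** In step 3 the scores really are correlated when ρ > 0. The fault is in reading that correlation as an effect of treatment.

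**Descriptive results.** Means or medians will be reported, so a fall in burden could be seen. It would still be untested.

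**QOL-AD.** It is a main outcome, and Table 1 includes the carer's report under it, so the family version may already have a pre/post test. The gap is certain only for burden and mutuality.

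**Importance.** The carer analysis is additional to the main outcomes and does not affect the conclusion on depression. This stands and limits the severity.

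**Conclusion.** Wrong as written; it should be fixed. The certain part rests on the text and on algebra alone: the hypothesis that burden falls and mutuality rises has no test, because a correlation across dyads does not register a common shift. The conditional part assumes that scores and not changes are correlated. Then, with 12 dyads, ρ = 0.5 and ICC 0.7 to 0.8, about 20 to 26% of single-visit correlations would be significant although no carer changed. That share runs from 5% at ρ = 0 to 51% at ρ = 0.7 (ICC 0.8). Both ρ and the ICC are assumptions.

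**What to change.** In Section 2.5:

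1. Test within-carer change from session 0 to the final session, and from session 0 to week 24, in the Zarit burden inventory and the mutuality scale. Add the QOL-AD family version if the main-outcome test does not already cover it. Use a paired t-test or a Wilcoxon signed-rank test. Do not carry over the Mann–Whitney U test named for the patient outcomes, which is for independent samples.
2. Then correlate carer change with patient change, one value per dyad. If all visits are to be used, use a within-dyad repeated-measures correlation.
3. Report the coefficient with its confidence interval and describe it as an association.

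The cost is a few sentences; Table 1 already schedules the data. The drawback is imprecision with 8 to 12 dyads. For an illustrative r of 0.5, the Fisher interval tanh(0.549 ± 1.96/√(n − 3)) runs from −0.10 to 0.83 with 12 dyads and from −0.32 to 0.89 with 8.

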## 3. Discussion

Depression in dementia can be treated with the use of psychosocial interventions, psychotherapy being part of this category. Any therapeutic approach that is used to work with PWD should be flexible, person-centred, and creative, in order to meet the needs of the person, as it has been well-underlined by Kitwood and followers [103,104]. These qualities are already central in GT and testify to the suitability of the approach for working with this population.

The design of this study mainly followed indications for the development of a SCED in GT, as recommended by GT authors with experience in research [70,105]. The aim of observing the effectiveness of the approach has been enriched by considering the context of the experience of living with dementia, which inevitably includes informal carers, who are often family members. Therefore, the benefits of receiving GT as treatment should also be observed from the perspective of the main family carer. This added aspect is in line with the GT field principle, i.e., that the embodied learning from the therapeutic “dance” can elicit relational adaptations (a *new dance*) in the family system.

Providing psychotherapeutic support from the earliest stages of dementia allows the patients to cope with the disease from the very beginning, integrating it into their lives and becoming protagonists of the future therapeutic choices. A grieving reaction, accompanied by an emotional crisis, which may include depression, may be experienced from the moment of diagnosis [106], as a response to it, or even before diagnosis [107], as the person’s life begins to be affected by the initial symptoms of dementia. The support received through a psychotherapeutic intervention can help the person to cope with losses, in order to create continuous new adaptations. GT’s holistic approach makes it possible to undertake a pathway to support the physiological, emotional, and cognitive ground of the patient that may be disrupted by the dementia condition.

It is expected that the results obtained from this research can submit significant data to support the impact between pre/post improvement, as well as whether the observed changes are clinically significant. It will be possible to review the attribution of these changes to the Gestalt therapeutic work.

An indirect effect on the family carers may be observed, as a result of the researched intervention, which may manifest in a reduction of their stress levels or emotional burden and, consequently, the improvement of the relationship with those they care for.

The statistical comparison strengthens the present evidence-based study on the efficacy of GT with people in these circumstances and opens a whole field of work and possibilities for undertaking future studies.

